# **Methods**

Study design:

A Cluster randomised incomplete stepped wedge trial for multiple standards on obstetric Care will be applied to assess the impact of using standards-based audit on compliance with defined standards for emergency obstetric and newborn care in Malawi. To appropriately reflect the diversity of expert opinion and disciplinary perspectives, a set of standards around emergency obstetric and newborn care were developed using a systematic, participatory process in accordance with WHO process of developing guidelines^15^ . The standards were mainly developed to address the common obstetric and newborn causes of death in low resource settings (cite). There are 25 standards in 7 groups (subsequently referred to as Standards Groups A, B, C, D, E, F and G) which have been defined (Appendix 1)

A total of 44 facilities are included in the design comprising of 10 designated to provide Comprehensive emergency obstetric care CEmOC and 34 facilities designated to provide basic emergency obstetric care (BEmOC) health facilities. Each participating facility is a cluster, and each facility will implement two periods of standards-based audit cycles. Each audit cycle comprises three months (a quarter): an assessment month, a month for action to address issues and a re-assessment month. Each of the ten CEmOC facilities will complete two standards-based audits in each quarter (four standards in total) and each of the 34 BEmOC facilities will complete one standards-based audits in each quarter (two standards in total).

Each standard assessed will be assessed using the incomplete stepped wedge design shown in Figure 1. Up to three facilities will be assigned to each sequence.

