**Randomisation**

Facilities have been randomised to three strata of 14 or 15 facilities, with each stratum including 2 or 3 CEmOC facilities. The stratum assigned determines the month in which the first audit cycle will be commenced (July, August, and September) in the facility. Randomisation was done using a Stata program using the runiform function. The randomisation was as balanced as possible within districts and facility type.

Three training workshops will be conducted for health care providers from each participating facility, before commencing the first audit cycle. There will be three workshops, one for health care providers in each stratum. During these workshops staff will be trained in the conduct of standard based audits. During the workshop they will also identify standards of most relevance to their facility which can be audited. Staff from each CEmOC facility will be asked to select 6 such standards for which the facility usually has at least 25 clients per month. Staff from BEmOC facilities will be asked to select 4 standards. They will rank these standards in terms of their importance to the facility.

The trial statistician will then assign standards to be audited within each facility in a manner which assigns the highest-ranking standards for each facility subject to the number in the stratum not exceeding six facilities for any given standard. In determining the standards to be audited at each facility priority will be given to the more popular standards, to maximise the number of individual standards for which there are close to 18 facilities auditing the standard following a balanced incomplete stepped wedge design.

The sequence in which standards are audited within each facility will be assigned using a Stata program using the runiform() function to randomise the facilities to quarters (1 or 2) for each standard. The allocation will be constrained to ensure that for each facility the appropriate number of standards are assigned to each quarter.

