**Sample size considerations**

For sample size calculations various parameters need to be specified. These include the intracluster correlation (ICC) and the cluster autocorrelation (CAC). The ICC refers to the correlation between values from individuals in the same cluster on the same occasion. The CAC measures the correlation between means within the same cluster at different times. It is assumed that data for each standard are collected according to the incomplete stepped wedge design shown in Figure 1, with three clusters following each sequence in the design. Sample size calculations were performed to determine differences detectable using the Rshiny app which was developed by [name], a Professor of Biostatistics whose research is focused on the design and analysis of stepped wedge trials (available at: <https://clusterrcts.shinyapps.io/rshinyapp/>).

Table 4 indicates the percentage change in compliance for the standard that is detectable for a single standard, with either 80% or 90% power, an ICC of either 0.1 or 0.2, and a CAC of 0.8 or 0.5 using a sample of 25 clients for each assessment month in each cluster. These calculations focused on the proportion of respondents who deemed the standard to have been achieved as a binary response, assuming that the initial compliance level for the standard is 50%.

**Table 4 Differences detectable (percentage) for using an incomplete stepped wedge design with specified number of facilities conducting a standards-based audit in a balanced incomplete stepped wedge design**

| **Sample size for each facility-month** | **Number of facilities doing standards-based audit** | **ICC** | **CAC** | **Power** | |
| --- | --- | --- | --- | --- | --- |
|  |  |  |  | **80%** | **90%** |
| 25 | 12 | 0.1 | 0.5 | 21.1% | 24.0% |
|  |  |  | 0.8 | 18.3% | 20.9% |
|  |  | 0.2 | 0.5 | 26.0% | 29.3% |
|  |  |  | 0.8 | 20.9% | 23.9% |
| 25 | 18 | 0.1 | 0.5 | 17.5% | 20.0% |
|  |  |  | 0.8 | 15.2% | 17.5% |
|  |  | 0.2 | 0.5 | 21.6% | 24.7% |
|  |  |  | 0.8 | 17.5% | 20.0% |
| 10 | 18 | 0.1 | 0.5 | 21.7% | 24.7% |
|  |  |  | 0.8 | 20.5% | 23.5% |
|  |  | 0.2 | 0.5 | 25.6% | 28.9% |
|  |  |  | 0.8 | 23.0% | 26.1% |

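### The quarter draw is balanced within each facility but not within each standard and stratum, so standards audited by few facilities can lose precision needlessly

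*Protocol*

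**What the plan says.** Four statements in the protocol bear on how facilities are split between the two quarters for a given standard.

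- **Randomisation, the draw.** A Stata program is to "randomise the facilities to quarters (1 or 2) for each standard". The only restriction named is: "The allocation will be constrained to ensure that for each facility the appropriate number of standards are assigned to each quarter".
- **Randomisation, the choice of standards.** The statistician assigns standards by rank, "subject to the number in the stratum not exceeding six facilities for any given standard", and aims for as many standards as possible with "close to 18 facilities auditing the standard following a balanced incomplete stepped wedge design".
- **Methods, Study design.** "Up to three facilities will be assigned to each sequence". Each CEmOC facility audits four standards, two per quarter. Each BEmOC facility audits two, one per quarter.
- **Sample size considerations.** Table 4 is computed "with three clusters following each sequence in the design", that is, 18 facilities over six sequences, with a smaller row for 12 facilities.

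A balanced layout is therefore the stated aim and the basis of Table 4. The sentence that defines the draw restricts it only within facility.

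**The concern.** In Figure 1, sequences 1 to 3 are the quarter-1 audits and sequences 4 to 6 the quarter-2 audits, one of each per stratum. The effect for a standard is separated from calendar month largely by comparing facilities of one stratum that audit it in different quarters. If nearly all of them fall in the same quarter, that comparison weakens.

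The named restriction fixes how many of a facility's standards fall in each quarter. It does not fix how many facilities fall in each quarter for a given standard. Read literally, each facility's quarter for that standard is 50:50 and independent of the other facilities. What is at stake is the precision of the per-standard estimates, which are the secondary outcome and the quantity that Table 4 describes.

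**Working it through.** **Inputs.** From the protocol: the Figure 1 layout, 25 clients per facility-month, ICC 0.1 or 0.2, CAC 0.5 or 0.8, baseline compliance 50%, power 80% or 90%. Assumed: two-sided 5% significance, which is not stated for the sample size but fits the planned 95% intervals and reproduces Table 4.

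**1. Reproducing Table 4.** Model: eight fixed month effects, a treatment effect, and random cluster and cluster-by-month effects. The three monthly means of a facility have covariance s²[ICC·CAC·J + (ICC(1−CAC) + (1−ICC)/25)·I], where s² is the average of p0(1−p0) and p1(1−p1). The detectable difference solves d = (1.960 + 0.842)·SE for 80% power.

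For ICC 0.2 and CAC 0.5 the shared term is 0.2 × 0.5 = 0.100 and the added diagonal term is 0.100 + 0.8/25 = 0.132. At d = 0.216, s² = (0.250 + 0.716 × 0.284)/2 = 0.227. With three facilities per sequence the solution is 21.6%, as in Table 4. All 16 figures in the 25-client rows agree within 0.2 points. The 10-client rows come out 0.5 to 1.7 points below the stated values; nothing here uses them.

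**2. Which splits the rules allow, per standard and stratum.**

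| Facilities in stratum | Facility rule only | With the cap of three per sequence |
| --- | --- | --- |
| 6 | any split; 3:3 has probability 20/64 = 31% | 3:3 forced |
| 5 | any split | 3:2 or 2:3 forced |
| 4 | any split | 3:1, 2:2 or 1:3; 2:2 in 6/14 = 43% |
| 3 or fewer | any split | any split |

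With the facility rule alone, an 18-facility standard is 3:3 in all three strata with probability (20/64)³ = 3.1%. A simulated stratum of 3 CEmOC and 12 BEmOC facilities with six standards gave 31.1% for a single standard, which confirms the binomial figure. With the cap, a 12-facility standard (four per stratum) is 2:2 in all three strata with probability (6/14)³ = 7.9%.

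**3. Loss of precision, fixed months.** Increase in SE over k/2 facilities per sequence, where k is the number in the stratum. Ranges run over ICC 0.1 with CAC 0.8 and ICC 0.2 with CAC 0.5; the other two pairs in Table 4 are not covered.

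| Facilities | Cap applied? | Median | 90th percentile |
| --- | --- | --- | --- |
| 18 | yes | 0 | 0 |
| 18 | no | +3 to 4% | +11 to 13% |
| 12 | yes | about +3% | +7 to 10% |
| 12 | no | +5% | +22 to 32% |
| 9 | does not bind | +9 to 10% | +26 to 35% |
| 6 | does not bind | +17 to 25% | +52 to 78% |

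The 9-facility benchmark of 1.5 per sequence cannot be reached. The best feasible rule (2:1 or 1:2 in each stratum) itself averages about 3% above it, so part of that row is unavoidable.

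**4. Random months.** The Statistical Analysis section specifies random effects for month. The month variance is not given. For an assumed month SD of 2.5 to 10 percentage points at 50% compliance, the 90th-percentile loss for 6 facilities is about 1 to 11%. For 18 facilities without the cap, the median is 0.2 to 2.3% and the 90th percentile 0.6 to 6.7%. A very large month variance would bring back the fixed-month figures.

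**5. Primary outcome.** Every facility has exactly half its standards in each quarter. Summed over a stratum, the facility-standard pairs are therefore split exactly evenly, whatever happens within a single standard.

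**The case against.** A reader might infer that the balanced design behind Table 4 is not delivered, and that a full standard loses power. Without the cap, that reading has numbers behind it. At ICC 0.2 and CAC 0.5 the mean detectable difference for 18 facilities rises from 21.6% to 22.5%, and 68% of allocations exceed the 22% stated after Table 4. Mean power over the four ICC and CAC pairs falls to 74 to 76%. But Methods caps each sequence at three facilities, and Randomisation names a balanced design as the aim. With at most six facilities per stratum the cap forces 3:3, so the documents do not support that reading. The Stata program is not shown, and the draw for each standard may already be made evenly.

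A reader might also take the largest losses, for 6 or 9 facilities, as the size of the problem. Table 4 has no such rows, the protocol says the detectable difference grows with fewer clusters, and the planned random month effects shrink the losses considerably. Nor is it shown that many standards will be that small. There are 10 × 4 + 34 × 2 = 108 facility-standard slots, exactly 6 × 18, and popular standards get priority. The spread depends on workshop rankings that the protocol cannot contain.

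Finally, a reader might infer bias or harm to the primary outcome. Neither follows: the quarters are still drawn at random, and the pooled split is even by construction.

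These replies narrow the point without removing it. The cap is missing from the allocation rule, and even when applied it leaves standards with four or fewer facilities per stratum open to uneven splits.

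**Conclusion.** The point holds in a limited form and is minor. The allocation rule under Randomisation restricts the draw within facility only and omits the cap stated under Methods. With the cap, standards with five or six facilities per stratum are as balanced as they can be. Those with four can split 3:1, and those with three or fewer can split in any way.

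The consequence is an avoidable loss of precision in per-standard, secondary estimates. For the 12-facility row of Table 4, with the cap and fixed months, it is about 3% in SE at the median and 7 to 10% at the 90th percentile. Scaling the 80% power entries, which slightly overstates the change, 26.0% × 1.07 = 27.8% and 18.3% × 1.10 = 20.1%, or about two points at the unfavourable end. Smaller standards can lose more, but the protocol states no power for them.

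The sizes rest on 50:50 independent draws within a standard and on the fixed-month model that reproduces Table 4. Under the planned random-month model they are smaller, by an amount that depends on a month variance the protocol does not give.

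**What to change.** In the Randomisation section, add a second restriction to the quarter draw: within each standard and stratum, the numbers of facilities in quarter 1 and quarter 2 differ by at most one. With at most six facilities per stratum this implies at most three per sequence, so it also carries over the cap from Methods. Apply it jointly with the facility rule and draw at random among the allocations that meet both.

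Such an allocation always exists. Take the facilities and standards of a stratum as the two sides of a graph, with one edge per audit. Every facility has two or four edges. Join each standard with an odd count to one dummy facility; there is an even number of these standards, because the total number of edges is even. Every node is then even, and assigning quarters alternately along closed circuits splits every facility exactly and every standard to within one.

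Simple redrawing until both rules hold is practical. In the simulated stratum of six full standards, 0.39% of draws under the facility rule alone were balanced for all six, or about one in 256. The cost is a few lines in the allocation program before quarters are drawn, with no extra clients, data or staff. If the quarters have already been drawn, Table 4 can instead be recomputed for the allocation obtained.

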**Data Collection**

As indicated in Figure 1 each of the standards to be audited at a facility will be assessed during the first and third month of the audit cycle for that standard. In addition, it will also be assessed during the first month of the first audit cycle at the facility (if the audit cycle is in the second quarter) or during the last month of the second quarter (if the audit cycle is in the first quarter) but not during other study months. Tables 2 and 3 illustrate the assessments to be performed for standards audited within a CEmOC facility in stratum which is assigned to audit for standards denoted as standards A, B, C and D, and a BEmOC facility in stratum II which is assigned to audit for standards denoted as standards E and F.

**Table 2: Timing of assessments for a CEmOC facility in Stratum I at which standards A, B, C and D are audited**

| Representation | Standard | Quarter 1 | | | Quarter 2 | | |
| --- | --- | --- | --- | --- | --- | --- | --- |
|  |  | July | Aug | Sept | Oct | Nov | Dec |
| By standard | A | X(a) |  | X(a) |  |  | X(a) |
|  | B | X(b) |  |  | X(b) |  | X(b) |
|  | C | X(c) |  | X(c) |  |  | X(c) |
|  | D | X(d) |  |  | X(d) |  | X(d) |
|  |  |  |  |  |  |  |  |
| As a facility | A, B, C and D | X(a,b,c,d) | A | X(a,c) | X(b,d) | B | X(a,b,c,d) |

Grey shaded boxes represent action being taken to address the standard being considered in that quarter. X(a) indicates that data for Standard A will be collected in that month, X(b), X(c) and X(d) are similarly defined

X(a,b,c,d) indicates that data for Standards A, B, C and D will be collected in that month

**Table 3: Timing of assessments for a BEmOC facility in Stratum II at which standards E and F are audited**

| Standard | Quarter 1 | | | Quarter 2 | | |
| --- | --- | --- | --- | --- | --- | --- |
|  | Aug | Sept | Oct | Nov | Dec | Jan |
| E | X(e) |  | X(e) |  |  | X(e) |
| F | X(f) |  |  | X(f) |  | X(f) |

Grey shaded boxes represent action being taken to address the standard being considered in that quarter. X(e) indicates that data for Standard E will be collected in that month, X(f) is similarly defined

Data for each standard will be collected by staff within the facility using a standard data collection tool, to obtain data for 25 clients within the relevant month either by conducting an exit interview or by extracting data from registers, case notes or partographs within facilities. When the number of eligible participants in the month is not expected to exceed 50 a consecutive sample of eligible clients within the facility will be obtained until the required number of 25 is reached. When more than 50 clients are anticipated systematic random sampling will be used to obtain the sample.

**Eligibility**

*Participant inclusion criteria*

- Clusters: 43 healthcare facilities providing emergency obstetric and newborn care within five districts in Malawi.
- Clients: women and their newborns who attend the study facilities for obstetric / newborn care addressed by the standard being assessed that month

**Participant type**

- Women and / or their newborns receiving obstetric or newborn care

**Target number of participants**

For each standard audited at a facility it is anticipated that care received by 25 clients will be assessed in each of three study months (as illustrated in Figure 1 and Tables 2 and 3). At each of the ten participating CEmOC designated facilities four standards are to be audited, thus the total clients participating at each CEmOC is expected to be 300. At each of the thirty-three participating BEmOC designated facilities two standards are to be audited, thus the total clients participating at each BEmOC is expected to be 150. The total number of participants is thus expected to be 8,100.

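### The stated 8,100 participants are client-by-standard assessments: distinct clients number at most that and possibly far fewer, and the facility count behind the total conflicts within the protocol

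*Protocol*

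**What the plan says.** Protocol, Target number of participants, starts from 25 clients per standard in each of three months: "it is anticipated that care received by 25 clients will be assessed in each of three study months". It applies this to the comprehensive facilities, "At each of the ten participating CEmOC designated facilities four standards are to be audited", and concludes "thus the total clients participating at each CEmOC is expected to be 300". For the basic facilities it says "At each of the thirty-three participating BEmOC designated facilities two standards are to be audited", giving 150 each. The section ends: "The total number of participants is thus expected to be 8,100". Participant type defines participants as people: women, their newborns, or both.

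Three other places bear on whether that product counts people.

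- Eligibility admits "women and their newborns who attend the study facilities for obstetric / newborn care addressed by the standard being assessed that month". It has no exclusion for a client already sampled for another standard.
- The text below Table 3 sets sampling one standard at a time. Where no more than 50 eligible clients are expected in the month, "a consecutive sample of eligible clients within the facility will be obtained until the required number of 25 is reached"; above that, a systematic random sample is drawn.
- Tables 2 and 3 place several of a facility's standards in the same month.

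On the number of facilities, Study design, Study sites and Table 1 give 10 CEmOCs and 34 BEmOCs, 44 in all. Eligibility gives 43 clusters, and Target number of participants gives thirty-three BEmOCs.

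**The concern.** A total of standards x months x 25 equals a number of people only when every standard draws different clients. Nothing in the protocol requires that, and the standards make overlap likely. In Appendix 1, standards 1.2, 1.3, 2.1, 4.1 and 5.1 apply to essentially every woman in labour or giving birth. Standard 3.1 applies to uncomplicated births and 7.1 to every newborn. Two such standards, sampled consecutively from the same start date and source, would pick up largely the same women. Facility volumes are not given, but a site with fewer than 50 births in a month could not supply 50 different women for two all-births standards.

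Two things are at stake. First, the total may be reported as the number of women and newborns enrolled. Second, the primary outcome aggregates over standards, so one client could enter that analysis several times within a facility-month. The aggregate model in Statistical Analysis is described only as similar to the single-standard one, whose random terms are month, facility and their interaction, with district possible. A fuller analysis plan could add a client term, but only if repeated clients can be identified in the data.

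**Working it through.** **Inputs.** From Target number of participants: 25 clients, 3 months per standard, 10 CEmOCs with 4 standards each, BEmOCs with 2 each. BEmOC count: 34 (Study design, Study sites, Table 1) or 33 (Target number of participants). Standards per month: Tables 2 and 3. Cap of six facilities per stratum for any standard, with three strata: Randomisation.

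**1. The plan's own figure.**
- CEmOC: 4 x 3 x 25 = 300. BEmOC: 2 x 3 x 25 = 150.
- With 34 BEmOCs: 10 x 300 + 34 x 150 = 3,000 + 5,100 = 8,100, as stated.
- With the 33 written in that section: 3,000 + 4,950 = 7,950, which is 150 short (1.9%).

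**2. Standards sharing a facility-month.**

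| Facility | Month 1 | Month 3 | Month 4 | Month 6 | Assessments | Distinct clients if overlap is complete |
| --- | --- | --- | --- | --- | --- | --- |
| CEmOC | 4 | 2 | 2 | 4 | 12 x 25 = 300 | 4 x 25 = 100 |
| BEmOC | 2 | 1 | 1 | 2 | 6 x 25 = 150 | 4 x 25 = 100 |

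**3. Lower bound from within-month overlap.**
- 44 facilities: 44 x 4 x 25 = 4,400, which is 54% of 8,100.
- 43 facilities: 43 x 4 x 25 = 4,300, which is 54% of 7,950.

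**4. Does the assignment rule allow that bound?** There are 10 x 4 + 34 x 2 = 108 facility-standard slots. Each standard can fill at most 6 x 3 = 18.
- Counting seven birth-related standards (1.2, 1.3, 2.1, 3.1, 4.1, 5.1, 7.1): 7 x 18 = 126 places, enough for 108 slots.
- Counting only the five all-births standards: 5 x 18 = 90 places, leaving 18 slots. Put in pairs into nine BEmOCs with no overlap there, each such site has 150 distinct clients instead of 100. The bound becomes 4,400 + 9 x 50 = 4,850, which is 60% of 8,100.

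**5. Between the bounds.** The protocol gives no overlap rate. Assuming a fraction f of the possible overlap occurs, distinct clients = 8,100 - f x (8,100 - 4,400), with 44 facilities:

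| f | Distinct clients |
| --- | --- |
| 0 | 8,100 |
| 0.25 | 7,175 |
| 0.50 | 6,250 |
| 0.75 | 5,325 |
| 1 | 4,400 |

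**The case against.** The strongest reply is that 4,400 is an extreme. It needs every standard at every facility to be sampled on the same clients. Staff choose and rank the standards, so the mix is unknown. The cap limits how many facilities can share the all-births standards. Standard 3.1 excludes complicated births. Standard 7.1 concerns the baby, who may count as a separate participant from her mother. Systematic sampling above 50 clients, and the choice between exit interviews and records, would also thin the overlap. All of this stands: it limits the size of the point but does not turn 8,100 into a count of people.

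Nor is 4,400 a strict minimum. It covers overlap within a month only, so a woman sampled for the antenatal standard 4.5 and later for a birth standard is outside it. It also assumes that 25 clients are always reached, whereas Sample size considerations allows for standards with fewer.

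A reader might infer that the power statement fails. It does not: Table 4 concerns one standard with 25 clients per facility-month, where a client sampled for another standard adds no duplicate.

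A reader might also infer that overlap is confined to the first and last months, which are wholly control and wholly intervention. Table 2 shows CEmOCs also assessing two standards together in months 3 and 4.

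Finally, one might ask for different clients for each standard. The protocol gives no ground for requiring that, and it has a cost: a standard would be sampled from a different part of the month when it shares the month than when it is assessed alone.

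**Conclusion.** The point holds as an error of labelling in the protocol's own participant number, together with a conflict in the facility count. The figures 300, 150 and 8,100 are client-standard assessments. Distinct clients will be at most the stated total and could be substantially fewer. The extreme within-month bound is 4,400 with 44 facilities (4,300 with 43), or about 4,850 with 44 facilities if only the five all-births standards overlap.

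These bounds assume 25 clients at every assessment and no overlap between months. The 4,850 also treats the remaining standards as not overlapping with one another. None of them is an expected value, and the protocol does not allow one to be calculated.

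The single-standard analyses and Table 4 are unaffected. The effect on the precision of the aggregated primary estimate has not been quantified and is probably small.

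**What to change.** - In Target number of participants, call 300, 150 and the total client-standard assessments. Say that distinct clients will be no more than this and may be substantially fewer.
- Before restating any total, reconcile 33 with 34 BEmOCs and 43 with 44 clusters across Study design, Study sites, Table 1, Eligibility and Target number of participants. With 33 BEmOCs the total is 7,950; with 34 it is 8,100.
- In Data Collection, state that a client may contribute to more than one standard.
- Record one study number per client on the data collection tool, if it does not already carry one. Distinct clients can then be reported, and repeated clients allowed for in the aggregated primary analysis.

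The cost is a few sentences and at most one field on the existing tool. The sampling procedure does not change. The reported number of people may fall below the number of assessments.
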